**Fig. 1 Fig1:**
[figure not shown]
Image of electrode placement in the thoracolumbar region

**Fig. 2 Fig2:**
[figure not shown]
Image of the portable TENS equipment

#### Criteria for discontinuing or modifying allocated interventions {11b}

The criteria for discontinuation are any medical complications during delivery or at the request of the participant. The women can also withdraw their consent prior to the publication of the results.

#### Strategies to improve adherence to interventions {11c}

As this is an intervention that happens only during labor, the researchers will explain in detail the procedure for participating in the project and the need for data collection after delivery.

#### Relevant concomitant care permitted or prohibited during the trial {11d}

During the protocol, oral and intravenous medications indicated by the physician are allowed, except for analgesics. Analgesic medications are not part of the hospital protocol, following government recommendations, so there will be no harm to the participants. Maternal mobility, bathing, and total freedom for the parturients in labor are allowed, as recommended by the WHO.

#### Provisios for posttrial care {30}

Researchers are responsible for any harm that occurs as a result of the study. Thus, researchers will provide participants with the health care needs that may arise as a direct consequence of trial participation.

### Outcomes {12}

#### Primary outcome measure

The primary outcome measure is change in the visual analog scale (VAS) from baseline to immediately after the intervention. The VAS is a simple one-dimensional instrument, used worldwide to assess pain intensity. It is characterized by a 10-cm-long horizontal line, where 0 represents no pain and 10 the worst imaginable or severe pain. They will be evaluated before the intervention and immediately after the intervention. All measurements will be performed in the period between uterine contractions.

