### Participant timeline {13}

Initially, volunteers will be numbered to avoid the risk of being identified. Soon after admission to the hospital, they will answer the standard anamnesis composed of questions about gynecological, obstetric, and health history, lasting approximately 10 min.

Before starting the intervention, the volunteer will be asked to mark the intensity of her pain at the moment on the VAS line. Immediately after and 30 min and 1 h after the interventions with the use of massage, TENS, or placebo, the request for pain intensity indication will be repeated.

After 12 to 24 h after the end of delivery, the volunteer will be visited by the researcher in the rooming-in and will be instructed to answer the intensity of pain in the VAS at this time, in addition to answering the QESP questionnaire. Then, birth and newborn data will be collected from the medical records.

The schematic diagram of the participant’s timeline can be seen in Fig. 3.

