### Sample size {14}

Based on a previous study by Báez-Suárez et al. [14], considering a difference between groups of 1.5 in VAS and a standard deviation of 1.61, considering an alpha of 0.05 and the power of the test of 0.80, the minimum sample size in each group is 36 participants.

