## Statistical methods

### Statistical methods for primary and secondary outcomes {20a}

Obstetric, gynecological, sociodemographic data, among others, will be compiled and collected using the statistical program Statistical Package for Social Sciences (SPSS Statistics version 23) and tabulated in the Excel program. The Shapiro-Wilk test will be applied to test the normality of the data, whether the data follow a normal distribution or follow a non-normal distribution.

The data will be presented to the normality of these, according to the quantitative variables that are normally distributed and continuously will be presented as mean (standard deviation). Continuous quantitative variables without normal distribution will be presented in median (interquartile range). Categorical variables will be assessed as frequencies and percentages.

For parametric data, a comparison between the groups will be carried out using the analysis of variance (ANOVA) test. Significance values lower than 0.05, at the 95% confidence interval, will be interpreted as statistically significant. The clinical relevance of the recorded values will be confirmed through effect size calculations (Cohen *d*) based on significant differences. The following effects will be taken into account: 0.00 to 0.49, low; 0.50 to 0.79, medium; and above 0.80, 312 high [25].

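### The primary VAS change would be compared by unadjusted ANOVA after a normality check, although baseline VAS is collected; one baseline-adjusted model stated in advance would be more precise and would fix the test

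*Protocol article*

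**What the plan says.** The Protocol article, under Primary outcome measure, states: "The primary outcome measure is change in the visual analog scale (VAS) from baseline to immediately after the intervention". The baseline value is part of the planned data. The same section says "They will be evaluated before the intervention and immediately after the intervention", and Participant timeline {13} confirms it: "Before starting the intervention, the volunteer will be asked to mark the intensity of her pain at the moment on the VAS line".

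Statistical methods for primary and secondary outcomes {20a} says "The Shapiro-Wilk test will be applied to test the normality of the data". It gives a descriptive summary for either result: mean and SD if normal, median and interquartile range if not. For the comparison between groups it gives one method: "For parametric data, a comparison between the groups will be carried out using the analysis of variance (ANOVA) test". No covariate is named, and no test is named for data that fail the normality check. The section on additional analyses {20b} plans none.

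Sample size {14} works from "considering a difference between groups of 1.5 in VAS and a standard deviation of 1.61", and "considering an alpha of 0.05 and the power of the test of 0.80", and concludes that "the minimum sample size in each group is 36 participants". It does not say whether 1.61 is the SD of a single VAS reading or of the change, and it makes no allowance for baseline adjustment.

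**The concern.** Two features of the primary analysis could be better fixed.

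First, subtracting the baseline amounts to assuming that post-intervention pain moves one-for-one with baseline pain. Where the true slope is below 1, the change score over-corrects and carries avoidable noise from the baseline reading. Fitting the slope removes that noise without another patient or measurement.

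Second, the between-group test is tied to a normality result that will be known only once the data are in. The VAS is bounded at 0 and 10, so its change may well fail Shapiro-Wilk. The text covers that event for description but not for comparison, so the test of the primary outcome would be chosen after the data had been seen. At stake are the width of the reported interval and whether the primary test is settled in advance. The validity of the randomised comparison is not at stake.

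**Working it through.** **Inputs.** Difference 1.5, SD 1.61, alpha 0.05 (taken as two-sided, since the article does not say), power 0.80 and 36 per group, all from Sample size {14}. The baseline-to-post correlation r is not in the documents; 0.3, 0.5 and 0.7 are assumed, with 0 as an extreme.

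**1. The plan's own figure.** n per group = 2 × [1.61 × (1.960 + 0.842) / 1.5]² = 18.08, so 19, not 36. The stated 36 is close to 2 × 18.08, or to a change score with SD 1.61 × √2 (37 per group). The article states neither. This mismatch is a separate matter and does not affect the present point.

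**2. Power at 36 per group, if 1.61 is the SD of change.** SE of a pairwise difference = 1.61 × √(2/36) = 0.379. Then 1.5/0.379 − 1.960 ≈ 1.99, giving power of about 97.7%.

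**3. Variance of the two analyses.** With a common within-group SD s before and after:

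- change score: 2s²(1 − r)
- baseline-adjusted: s²(1 − r²)
- ratio, adjusted to change: (1 + r)/2

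| r (assumed) | variance ratio | square root | CI narrower by |
|---|---|---|---|
| 0.3 | 0.65 | 0.806 | 19% |
| 0.5 | 0.75 | 0.866 | 13% |
| 0.7 | 0.85 | 0.922 | 8% |

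If 1.61 is the SD of change, the 95% half-width for a pairwise difference is 1.960 × 0.379 ≈ 0.74 for the change score. After adjustment it is 0.74 × 0.806 ≈ 0.60, 0.74 × 0.866 ≈ 0.64 and 0.74 × 0.922 ≈ 0.69 at r = 0.3, 0.5 and 0.7.

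**4. If variances differ.** With baseline SD s₀ and post SD s₁, the change-score variance minus the adjusted variance is s₀² + s₁² − 2r s₀s₁ − s₁²(1 − r²) = (s₀ − r s₁)². This is never negative. The direction of the gain therefore does not need equal variances, only its size does. The cost is one residual degree of freedom out of 108 − 3 = 105.

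**5. What this does to power at 36 per group.**

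| Reading of 1.61 | r | change score | adjusted |
|---|---|---|---|
| SD of change | 0.3 | 97.7% | 99.8% |
| SD of change | 0.5 | 97.7% | 99.5% |
| SD of change | 0.7 | 97.7% | 99.0% |
| single-time SD | 0 | 79.8% | 97.7% |
| single-time SD | 0.3 | 91.6% | 98.6% |
| single-time SD | 0.5 | 97.7% | 99.5% |

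Under the single-time reading the change SD is 1.61 × √(2(1 − r)) and the adjusted SD is 1.61 × √(1 − r²).

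**6. The normality check.** Setting the two halves of {20a} side by side gives: normal data, a summary and a test; non-normal data, a summary and no test. No arithmetic applies.

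**The case against.** The strongest reply is that nothing here is invalid. Change-score ANOVA in a randomised trial gives an unbiased comparison, and defining an outcome as a change is not an error. That stands, and it sets the weight of the point.

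A reader might go further and say that chance baseline imbalance biases the result as an additional harm. Taking 1.61 as a single-time SD, a one-SE imbalance of 0.379 moves the change-score contrast by 0.379 × (1 − r), which is 0.27, 0.19 or 0.11 at r = 0.3, 0.5 or 0.7. This is not a second loss. The change-score variance splits as 2s²(1 − r) = s²(1 − r²) + s²(1 − r)², and at r = 0.5 that is 1.00 = 0.75 + 0.25 in units of s². The imbalance term is already inside the wider change-score interval. The shift also depends on an unstated r and on one reading of 1.61.

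A reader might also infer that the lost precision threatens the primary conclusion. The stated inputs do not show that. Power is below 90% only if 1.61 is a single-time SD and r is well under 0.3.

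The last reply is that a condensed article may leave the fallback test to a statistical analysis plan that is not shown. So it cannot be said that no fallback exists anywhere. It is also an inference, from the outcome definition read with {20a}, that ANOVA would be run on the change score. What stands is that the published text makes the test conditional on a data-driven check and fills only one branch.

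**Conclusion.** The point holds as a free improvement, not as an error that invalidates the trial. Adjusting for a baseline that is already collected would narrow the primary interval by about 19%, 13% or 8% at r = 0.3, 0.5 or 0.7. This assumes equal variances before and after, and values of r that the documents do not supply. On the stated inputs the benefit is mainly a tighter estimate, since power is already about 97.7% if 1.61 is the SD of change. It would be a material gain in power only under the single-time reading with low r.

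The second part does not depend on r. As written, the primary test is selected by a normality result and is unstated if that result is unfavourable. One model named in advance settles both parts. It does not settle which pairwise comparison among the three groups is primary, which is a separate question.

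**What to change.** Replace the conditional wording for the VAS outcomes with one statement:

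- The primary analysis is a linear model of VAS immediately after the intervention on group (three levels) and baseline VAS, fitted whatever the normality test shows.
- Standard errors come from one method named in advance, for example HC3 robust. Leaving a choice between methods would reopen what the change is meant to close.
- Adjusted between-group mean differences are reported with 95% confidence intervals.
- The same model is used for the VAS at 30 min, at 1 h and at 12–24 h postpartum.
- Shapiro-Wilk no longer decides the test, and a rank-based comparison is kept only as a sensitivity analysis.

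The outcome definition can stay as it is. With baseline in the model, regressing the change or the post-intervention value gives the same group differences.

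No further patients, visits or data are needed. The sponsor should confirm that the named SPSS version provides the chosen standard-error method. Recruitment began in April 2020, and the amendments section {25} requires a formal amendment, ethics approval and a registry update for major modifications. The sponsor should judge whether this change counts as one and should make it before outcome data are examined.

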#### Secondary outcome measures

The secondary outcomes include change in the visual analog scale (VAS) from baseline to 30 min and 1 h after the intervention and in the immediate postpartum period (12–24 h after labor).

The participant’s satisfaction with childbirth will also be evaluated using the Experience and Satisfaction with Childbirth Questionnaire (QESP). This is a self-report questionnaire, with a total of 104 questions, which refer to the expectations, experience, satisfaction, and quality of the woman’s experience in relation to labor, delivery, and immediate postpartum. It consists of questions divided into eight subscales: (1) conditions and care provided, (2) positive experience, (3) negative experience, (4) relaxation, (5) social support, (6) partner’s support, (7) concerns, and (8) postpartum. The higher the score obtained in each of the subscales, the more positive is the perception of women in the dimension assessed by the subscale. The administration time for this questionnaire is approximately 30 min [21]. The questionnaire will be applied in the immediate postpartum period (12–24 h after delivery).

After delivery, information on the type of delivery, total duration of delivery, and possible obstetric complications will be collected from the participants’ medical records. Newborn data will also be collected from medical records: weight, height, possible complications, and Apgar score in the first and fifth minutes.

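### The 12–24 h postpartum VAS reads as a change from a labor baseline; if the two scores are weakly correlated, this costs precision at one secondary time point

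*Protocol article*

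**What the plan says.** Under *Secondary outcome measures*, the protocol article lists "change in the visual analog scale (VAS) from baseline to 30 min and 1 h after the intervention and in the immediate postpartum period", the last item being placed "in the immediate postpartum period (12–24 h after labor". The grammar is loose, but on the natural reading all three time points are changes from baseline.

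*Participant timeline {13}* describes the two measurements. For the baseline: "Before starting the intervention, the volunteer will be asked to mark the intensity of her pain at the moment on the VAS line". At the visit 12 to 24 h after delivery, the woman "will be instructed to answer the intensity of pain in the VAS at this time", and no subtraction is mentioned. The VAS time points in the Abstract stop at 1 h.

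Under *Primary outcome measure* a general condition is set: "All measurements will be performed in the period between uterine contractions". That condition has a clear meaning in labor.

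*Statistical methods {20a}* says that for parametric data "a comparison between the groups will be carried out using the analysis of variance (ANOVA) test". No baseline covariate is named.

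**The concern.** At 30 min and 1 h, a change from baseline still describes the course of labor pain. At 12–24 h postpartum, labor is over, so the change is pain after birth minus pain in active labor. Two things follow.

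- **Precision.** Subtracting a baseline helps only when it predicts the later score well enough. If it does not, the subtraction adds the baseline's variance and removes little noise.
- **Interpretation.** Pain is likely to fall in every arm because labor has ended. Listed beside the 30 min and 1 h changes, that fall could be taken for a continuing response to massage or TENS.

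At stake is the efficiency and labeling of one secondary comparison. The two sections also leave open whether the outcome is a change or a score.

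**Working it through.** **Inputs from the protocol.** 36 women per arm, "considering a difference between groups of 1.5 in VAS and a standard deviation of 1.61", and "considering an alpha of 0.05 and the power of the test of 0.80" (*Sample size {14}*). Two-sided alpha is taken.

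**Inputs not in the protocol, so assumed.** The correlation r between labor baseline and postpartum VAS, the SD at each time, and the use of 1.61 as the SD of a single score. The protocol does not say whether 1.61 refers to a score or to a change.

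**The plan's own figure.** n per group = 2 × (1.960 + 0.842)² × 1.61² / 1.5² = 18.1, so 19 (20 with the t distribution), not 36. With the variance doubled the formula gives 36.2. This mismatch is a separate matter, and nothing below depends on it.

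**Variance formulas.** Let k = SD(baseline) / SD(postpartum).

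- Change against score: 1 + k² − 2rk, which is 2(1 − r) when k = 1.
- ANCOVA against score: 1 − r².
- Change against ANCOVA when k = 1: 2(1 − r) / (1 − r²) = 2 / (1 + r).

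**Equal SDs (k = 1), SD 1.61, 36 per arm, one pairwise comparison** (power by normal approximation):

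| r | Change / score | Change / ANCOVA | Power for 1.5 points, change |
|---|---|---|---|
| 0 | 2.0 | 2.00 | 79.8% |
| 0.2 | 1.6 | 1.67 | 87.8% |
| 0.3 | 1.4 | 1.54 | 91.6% |
| 0.5 | 1.0 | 1.33 | 97.7% |
| 0.7 | 0.6 | 1.18 | 99.9% |

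The score alone has SE 1.61 × √(2/36) = 0.379 and 97.7% power for 1.5 points. For a 1.0-point difference, power is 75.0% with the score, against 46.2% with change at r = 0 and 54.9% at r = 0.2.

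**Effective sample size.** Relative to ANCOVA, 36 women analyzed by change carry the information of 36(1 + r)/2: 18 at r = 0, 23.4 at r = 0.3 and 27 at r = 0.5.

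**Detectable difference at 80% power.** This is SE × 2.84 (t quantiles 1.994 + 0.847 on 70 df).

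- Change: 0.5367 × 2.84 = 1.52 at r = 0, and 0.4490 × 2.84 = 1.28 at r = 0.3.
- ANCOVA: 0.3795 × 2.84 = 1.08 at r = 0, and 0.3620 × 2.84 = 1.03 at r = 0.3.

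**Unequal SDs.** At r = 0, change / score is 1.25 for k = 0.5, 3.25 for k = 1.5 and 5.0 for k = 2. Change is less precise than the score whenever r is below k/2.

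**Why the remedy does not depend on r or k.** Since 1 + k² − 2rk = (1 − r²) + (k − r)², the variance of change is never below that of ANCOVA. Since 1 − r² ≤ 1, neither is that of the raw score. The only offset is one degree of freedom.

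**The case against.** The strongest reply is that nothing here is invalid. Baseline precedes the intervention and allocation is random, so the expected between-arm difference in change equals that in the postpartum score. The fall due to the end of labor is common to all arms and cancels from the comparison. This stands in full. A reader might infer that a change score cannot show whether one arm has less pain after birth; it can, only less precisely.

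Second, the size rests on assumptions. A reader might take the two scores as nearly unrelated, or a doubling of variance as the ceiling. The protocol supports neither: it gives no correlation and no SD by time point. With equal SDs the penalty against the raw score vanishes at r = 0.5 and reverses above it; with unequal SDs the ratio can exceed 2. This stands too, so the results are shown as a range.

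Third, against the trial's own target of 1.5 points, change at r = 0 with equal SDs still has about 80% power. That is correct if 1.61 is the SD of a score. It limits the seriousness of the point but is no reason to forgo free precision.

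Fourth, the sentence may have been meant to list the postpartum VAS as a separate score, as the timeline suggests. That is possible, and is itself a reason to align the sections. Covariates may also be left to an analysis plan that is not shown, so the missing covariate is no fault in itself. The point is that the outcome definition, as written, points to the less efficient quantity.

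Finally, because 36 per group nearly follows from a doubled variance, a reader might infer that the sample size already allowed for an uncorrelated change score. The protocol does not say so.

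**Conclusion.** The point holds as one of precision and labeling, not of bias. On its natural reading, the protocol defines postpartum pain as change from a labor baseline, which conflicts with the plain description in the timeline. If the correlation is low, the comparison gives up information: with equal SDs, the variance is 2.0 to 1.33 times that of a baseline-adjusted analysis for r from 0 to 0.5. The actual factor is unknown, because the correlation and the time-specific SDs are not given. The within-arm fall would largely reflect the end of labor and is not evidence of treatment relief. One secondary time point is affected; the primary outcome is not.

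**What to change.** - In *Secondary outcome measures*, take the 12–24 h item out of the change-from-baseline list and define it as *VAS score at 12–24 h postpartum*. Label it postpartum pain, not labor pain relief.
- Compare arms by ANCOVA on that score, with the labor baseline VAS as covariate.
- Do not adjust for type of delivery, which arises after randomization; describe it by arm.
- Align *Secondary outcome measures* and *Participant timeline {13}* so that both describe the same quantity.

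The baseline VAS is already collected, so no new data are needed. The cost is one degree of freedom and a change of wording.

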**Methods:**

This is a randomized controlled clinical trial, with a non-probabilistic convenience sample, composed of women in the first active stage of labor, admitted to a public institution. The parturients will be divided into 3 groups: group 1 (*n* = 36) composed of parturients who will have continuous support and will be encouraged to walk, adopting different positions with the use of the Swiss ball and receiving back massage for 30 min; group 2 (*n* = 36) composed of parturients who will also have continuous support and will be encouraged to walk, adopt different positions using the Swiss ball, and will receive the application of TENS for 30 min; and group 3 (*n* = 36) composed of parturients who will have continuous support and will be encouraged to walk, adopting different positions with the use of the Swiss ball, and will receive placebo TENS application for 30 min. The outcomes evaluated in the study will be pain intensity assessed by the visual analog scale of pain applied before, immediately after, and 30 min and 1 h after the interventions; Experience and Satisfaction with Childbirth Questionnaire (QESP) applied 12 to 24 h after delivery; and data regarding delivery (type of delivery, total duration of labor, and possible obstetric complications) and neonate (weight, height, possible complications, Apgar score in the first and fifth minutes).

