### Objectives {7}

The aim of this randomized clinical trial is to verify the effects of non-pharmacological methods of pain relief added to the application of TENS on pain, satisfaction with childbirth, duration of labor, and the birth conditions of newborns.

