#### Intervention description {11a}

The intervention of the three groups will take place during the first active phase of labor, from admission, which occurs when the parturient has 4 cm of cervical dilation, until the beginning of the expulsive period. The three groups will receive continuous support from professionals, encouraging walking and the adoption of vertical postures (standard intervention). In addition, parturients in group 1 will be positioned on a Swiss ball to receive a massage in the dorsal region for 30 min. Classic massage movements will be used, such as superficial sliding, deep sliding, kneading, friction, and rolling. Almond oil will be used to facilitate manual maneuvers.

Women in group 2 will undergo a standard intervention plus an intervention using TENS electrostimulation using the portable Neurodyn equipment (IBRAMED-Indústria Brasileira de Equipamentos Médicos EIRELI, Brazil). The parturients will be positioned seated on the Swiss ball, and four silicone electrodes will be fixed with masking tape in the thoraco-lumbar region, at the levels of T10–L1 and S2–S4. A frequency of 100 Hz and a pulse width of 100μs will be used, with intensity depending on the sensitivity of each patient for 30 min [17] (Figs. 1 and 2. Women in group 3 will undergo standard intervention and placebo intervention. They will be positioned and have electrodes attached in a similar way to group 2. However, the equipment will remain with the intensity button deactivated, without current flow (Figs. 1 and 2).

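### Newborn weight and height are classed as outcomes although 30 minutes of treatment in term labor cannot change them; they belong in a descriptive table without a test

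*Protocol article*

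**What the plan says.** The protocol article lists the newborn variables twice. The Abstract (Methods) ends its list of outcomes with "neonate (weight, height, possible complications, Apgar score in the first and fifth minutes". The Secondary outcome measures section says: "Newborn data will also be collected from medical records: weight, height, possible complications, and Apgar score in the first and fifth minutes". Objectives {7} sets out to verify effects "on pain, satisfaction with childbirth, duration of labor, and the birth conditions of newborns". Nowhere are weight and height called baseline, descriptive or balance data.

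Section {20a} is headed as covering primary and secondary outcomes. It applies a Shapiro-Wilk screen and then states: "For parametric data, a comparison between the groups will be carried out using the analysis of variance (ANOVA) test". Values below 0.05 count as significant, and Cohen d is calculated for significant differences to confirm clinical relevance, with 0.50 to 0.79 labelled medium.

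On timing, Eligibility criteria {10} admits women in active labor at 37–42 weeks. Intervention description {11a} starts the intervention at admission, at 4 cm dilation. The component that differs between arms is massage, TENS or placebo TENS, and its length is 30 minutes (for TENS, "with intensity depending on the sensitivity of each patient for 30 min").

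**The concern.** An outcome is a variable that the allocated treatment might change. A term baby's weight and length are in effect settled before the mother is randomized, although they are measured after birth. They behave as baseline characteristics recorded late. A significance test on them asks only whether the arms happen to differ.

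Reading the result as an outcome can mislead in two ways. A significant difference could be taken as an effect on the newborn, with an effect size attached. A non-significant one, which is much more likely, could be taken as reassurance about newborn condition, although these two variables cannot show harm or benefit from the session. In both cases part of the newborn aim would be answered by variables that carry no information about it.

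**Working it through.** **Step 1: do the article's own rules reach these variables?**

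| Link | Where | Status |
|---|---|---|
| Weight and height are outcomes | Abstract (Methods); Secondary outcome measures | stated |
| The analysis section covers secondary outcomes | heading of {20a} | stated |
| Parametric data are compared by ANOVA at 0.05, with Cohen d if significant | {20a} | stated |
| Weight and height pass the normality screen | not in the document | assumption |
| Weight and height are tested | follows from the rows above | inferred |

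**Step 2: can allocation change them?** Entry is in active labor at 37–42 weeks, and the differing component lasts 30 minutes. No plausible effect on weight or length exists, so in the full randomized set the null hypothesis holds for both.

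**Step 3: chance of a spurious result.** Inputs are three arms of 36 (Abstract; Sample size {14}) and 0.05 per test ({20a}). The article gives no false-positive figure for these variables, so there is none to reproduce.

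- One variable: 0.05.
- Two variables, upper bound whatever their correlation: 0.05 + 0.05 = 0.10.
- Two independent variables: 1 − 0.95² = 1 − 0.9025 = 0.0975.
- Two correlated variables: simulated one-way ANOVA, 3 × 36, with no true difference. The correlations are assumptions, because the article gives none.

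| Assumed correlation | P(at least one p < 0.05), 20,000 trials | Repeat, 8,000 trials |
|---|---|---|
| 0 | 0.099 | 0.096 |
| 0.5 | 0.094 | 0.093 |
| 0.7 | 0.086 | 0.086 |
| 0.8 | 0.082 | 0.080 |

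The two runs agree within simulation error. The range is about 8–10%, so about 90% or more of trials would show no significant difference in either variable.

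**Step 4: what Cohen d would add.** With 2 and 105 degrees of freedom (3 − 1 and 108 − 3), the 5% critical value of F is 3.083. At that threshold the squared deviations of the three arm means, in units of the pooled within-arm variance, sum to 2 × 3.083 / 36 = 0.171. The smallest possible gap between the two most distant arms occurs when the other two means coincide. The sum is then (2/3)d², so d = √(1.5 × 0.171) = 0.51. With 36 per arm, any significant ANOVA thus comes with a largest pairwise d of at least 0.51, which the article's scale calls medium or higher. For a variable that treatment cannot move, that label would describe a chance or selection imbalance.

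**The case against.** **Testing is inferred.** The Secondary outcome measures section says only that the newborn data are collected, and {20a} names no newborn variable. A reader might infer that the article states that weight and height will be tested. It does not. That conclusion comes from joining the outcome lists to the heading and rule of {20a}, and an analysis plan that is not shown could assign them to description. This limits the strength of the point. What stands is the classification, which the article itself makes in two places.

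**Chance is not the only source of a difference.** A reader might infer that any significant difference must be a chance false positive. The document does not support that. Section {11b} allows discontinuation for medical complications and withdrawal of consent until the results are published, and {20c} expects that some data may be missing. If losses differ between arms, the women with data could differ in birth weight. That would still not be a treatment effect, but it would not be pure chance.

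**Misreading is not announced.** A reader might infer that the authors will credit a difference to TENS, or read a null result as newborn safety. No sentence says so. The aim's newborn term is left undefined, Apgar and complications stand beside weight and height, and the Discussion is about pain management.

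**The size is generic.** The 8–10% is just 0.05 applied to two null variables; any other such pair would give much the same. This is correct. The point depends on these two variables having no possible true positive, not on the percentage.

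**Conclusion.** The point holds as a minor one. The article classes two variables as outcomes that allocation cannot affect, and its analysis rule would compare them by ANOVA and attach Cohen d if they pass the normality screen. A significant difference would then mean chance imbalance or differential loss after randomization. A non-significant one would carry no information about newborn safety.

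If both are tested, the chance of at least one spurious result is at most about 10%. This figure assumes that both pass the screen, that each is tested once at 0.05, and that no differential loss occurs; such loss could raise it.

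The primary outcome, change in VAS pain, is unaffected. The point does not extend to Apgar, newborn complications, type of delivery or duration of labor, all of which could plausibly respond to treatment.

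**What to change.** In the Abstract and under Secondary outcome measures, take newborn weight and height out of the outcomes and call them descriptive characteristics: summarized by arm, with no significance test and no effect size. In Objectives {7}, or where the newborn outcomes are defined, state that the newborn part of the aim rests on Apgar score at the first and fifth minutes and on newborn complications.

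The cost is a few words. The same data are collected from the same records, two uninformative tests are dropped, and sample size and trial conduct do not change.
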